### Criteria for exclusion from analysis

All randomized participants will be included in the primary intention-to-treat (ITT) analysis. The criteria for the per-protocol (PP) population and data handling are mentioned in the following sections:

### Exclusion from PP analysis

Participants will be excluded from the PP analysis if they undergo fewer than 10 intervention sessions (50% of the planned treatment) without a medically justified reason. They will be excluded because insufficient exposure prevents the assessment of treatment efficacy.

Major protocol violations that critically affect efficacy evaluation, such as incorrect randomization, receiving the wrong intervention group assignment, or violation of the key inclusion/exclusion criteria, will also lead to exclusion from PP analysis.

Additionally, missing the primary outcome (VAS score) at the post-treatment (day 20) time point results in exclusion from the PP analysis.

### Handling of missing data

For the primary ITT analysis, missing data will be handled using multiple imputation by chained equations (MICE). The details are described in the statistical plan.

Sensitivity analyses will be used to compare the results of the imputed ITT population with those of the complete-case PP population to assess the robustness of the results.

### Interventions

#### Quality control for acupuncture

All acupuncturists have at least 10 years of clinical experience and possess 40 h of standardized training on both YLDJJ and conventional acupuncture protocols, including video-based assessment for point selection and needling technique. For quality control, a third-party expert will randomly select 10% of sessions to verify consistency. Additionally, separate personnel will be assigned to provide daily treatment reminders to the participants.

#### Experimental group: Yuan-Luo Da-Jie-Jing (YLDJJ) acupuncture + rTMS

The acupuncture procedure will be conducted based on the following sequence:

Acupoint selection and sequence: Yuan-Source points and Luo-Connecting points of the 12 regular meridians will be needled sequentially, with alternation between affected and unaffected sides. The specific order is as follows: Taiyuan (LU 9, Lung Yuan-Source) → Pianli (LI 6, Large Intestine Luo-Connecting) → Chongyang (ST 42, Stomach Yuan-Source) → Gongsun (SP 4, Spleen Luo-Connecting) → Shenmen (HT 7, Heart Yuan-Source) → Zhizheng (SI 7, Small Intestine Luo-Connecting) → Jinggu (BL 64, Bladder Yuan-Source) → Dazhong (KI 4, Kidney Luo-Connecting) → Daling (PC 7, Pericardium Yuan-Source) → Waiguan (SJ 5, Triple Energizer Luo-Connecting) → Qiuxu (GB 40, Gallbladder Yuan-Source) → Ligou (LR 5, Liver Luo-Connecting). The location and attributes are detailed in Table 1 and Figure 2.

**Table 1 tab1:** Acupoint localization and attributes for YLDJJ acupuncture.

Acupoint name	Code	Meridian	Specific point type	Localization (WHO standard)
Taiyuan	LU 9	Lung	Yuan-source	On the wrist, at the radial end of the transverse crease, in the depression lateral to the radial artery.
Pianli	LI 6	Large intestine	Luo-connecting	On the forearm, 3 cun proximal to LI5 (Yangxi), on the line connecting LI5 and LI11, between the radius and ulna.
Chongyang	ST42	Stomach	Yuan-source	On the dorsum of the foot, between the 2nd and 3rd metatarsal bones, in the depression distal to the base of the 2nd metatarsal bone, over the dorsalis pedis artery.
Gongsun	SP 4	Spleen	Luo-connecting	On the medial foot, distal and inferior to the base of the 1st metatarsal bone, in the depression at the border of the red and white skin.
Shenmen	HT 7	Heart	Yuan-source	On the wrist, at the ulnar end of the transverse wrist crease, in the depression radial to the tendon of the flexor carpi ulnaris.
Zhizheng	SI 7	Small intestine	Luo-connecting	On the forearm, 5 cun proximal to the dorsal wrist crease, on the line connecting SI5 (Wangu) and SI8 (Xiaohai), between the ulna and the tendon of the flexor carpi ulnaris.
Jinggu	BL 64	Bladder	Yuan-source	On the lateral foot, distal to the tuberosity of the 5th metatarsal bone, at the junction of the red and white skin.
Dazhong	KI 4	Kidney	Luo-connecting	On the medial foot, posterior and inferior to the medial malleolus, in the depression anterior to the Achilles tendon.
Daling	PC 7	Pericardium	Yuan-source	On the wrist, at the midpoint of the transverse wrist crease, between the tendons of the palmaris longus and flexor carpi radialis.
Waiguan	SJ 5	Triple energizer	Luo-connecting	On the forearm, 2 cun proximal to the dorsal wrist crease, between the radius and ulna.
Qiuxu	GB40	Gallbladder	Yuan-source	On the dorsum of the foot, anterior and inferior to the lateral malleolus, in the depression lateral to the tendon of the extensor digitorum longus.
Ligou	LR 5	Liver	Luo-connecting	On the leg, 5 cun above the tip of the medial malleolus, on the medial border of the tibia.

cun: Relative measurement based on the patient’s anatomy (e.g., the width of the thumb at the interphalangeal joint = 1 cun). Radial/Ulnar: Thumb side (radial)/little finger side (ulnar) of the arm. Medial/Lateral: Toward the midline (medial)/away from the midline (lateral) of the body. Proximal/Distal: Closer to the trunk (proximal)/farther from the trunk (distal).

**Figure 2 fig2:**
[figure not shown]
Acupoint illustration for YLDJJ acupuncture.

#### Acupuncture technique

Sterilized disposable stainless steel needles (0.30 mm × 40 mm, Hwato) will be employed. The insertion depth will range from 10 to 25 mm based on anatomical location. A standardized reinforcing-reducing manipulation will be applied, involving uniform lifting, thrusting, and rotating maneuvers at 60–90 cycles per minute for 20–30 s per acupoint to achieve deqi.

Deqi definition: Deqi is defined as a combination of subjective sensations reported by the patient (e.g., soreness, numbness, heaviness, and distension) and the objective sensation of needle grasp felt by the practitioner (34, 35). Needle retention: Needles will remain *in situ* for 30 min.

Treatment schedule: Sessions will be conducted once daily, 5 days per week, for a total of 20 sessions over 4 weeks. Each session will last approximately 40 min.

For rTMS, stimulation will be delivered to the contralateral M1 hand area using the Shenzhen Yingzhi M-50 apparatus. The M1 hand area will be identified using the international 10–20 EEG system for scalp electrode placement, with the target site at C3 (for right hemiparesis) or C4 (for left hemiparesis). The resting motor threshold (RMT) will be determined before the first treatment session to individualize stimulation intensity. Key parameters, including frequency, intensity, and pulse configuration, are summarized in Table 2. The schematic diagram of M1 is shown in Figure 3.

**Table 2 tab2:** Parameters for repetitive rTMS protocol.

Parameter	Specification
Device	Shenzhen Yingzhi liquid-cooled circulating M-50 Ultimale rTMS therapeutic apparatus
Stimulation site	Contralateral primary motor cortex hand area corresponding to the painful limb(M1)
Frequency	10 Hz
Intensity	80–120% of resting motor threshold
Trains per session	20
Pulses per train	1 pulses per train
Train duration	10 s
Inter-train interval	10 s
Total pulses/session	2,000
Session duration	19 min 50 s
Treatment schedule	Once daily for 20 consecutive days

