#### Acupuncture technique

Identical needles (0.30 mm × 40 mm) will be used for acupuncture. The insertion depth, manipulation to achieve deqi, deqi criterion, needle retention time (30 min), and treatment schedule (once daily, 20 sessions) will be standardized to match the procedures in the experimental group, leaving only the acupoint prescription as the major variable.

rTMS procedure:

The rTMS protocol (parameters, site, and schedule) is identical to that described for the experimental group.

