#### Control group 2: sham acupuncture + rTMS

Acupuncture technique:

Acupoint selection: The same set of 12 acupoints used in the experimental group will be used for the control group.

Sham needling technique: The non-penetrating Streitberger-type placebo needle (Asiamed) will be applied at each acupoint (36, 37). This device has a blunt tip that retracts into the handle upon contact with the skin, allowing insertion without piercing the skin. The needle will be fixed in place with an adhesive ring to mimic the appearance of a real needle.

Simulated deqi: To maintain blinding, the acupuncturist will gently manipulate the sham needle handle periodically without applying penetrating pressure and will ask open-ended questions about sensation, not mentioning specific deqi sensations.

Needle retention: The sham needles will remain in place for 30 min, matching the retention time in the active acupuncture groups.

Treatment schedule: The session frequency and duration (once daily, 20 sessions) will be identical to the other groups.

rTMS Procedure:

The rTMS protocol (parameters, site, and schedule) will be identical to that described for the experimental group.

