#### AE reporting and harms

AE documentation will follow CTCAE v5.0 for all events. Specific procedures for managing common AEs are as follows: For acupuncture, minor bleeding or hematoma will be managed with prolonged local pressure; syncope (needle fainting) will be managed by immediately withdrawing needles, placing the participant in a supine position, and monitoring vital signs. For rTMS, headaches will be managed with rest and non-opioid analgesics if necessary (recorded as rescue medication); in case of a seizure (despite excluding high-risk participants), stimulation will be stopped immediately, standard seizure first aid will be administered, and medical support will be sought. Expected AEs based on the literature and our pilot data include mild (19, 41), transient headache with rTMS (~10 to 15% incidence), and minor local bleeding/bruising with acupuncture (~5 to 10% incidence). For the primary safety analysis, the focus will be on clinically significant risks by including only grade ≥2 (moderate to severe) AEs. Serious adverse events (SAEs) will be events causing death, permanent/significant disability, permanent organ damage, or hospitalization/prolonged stay. In case of SAEs, researchers will immediately ensure participant safety and report it to the sponsor and ethics committee within 24 h. The trial center and blinded editor will jointly perform emergency unblinding due to SAEs. Researchers will determine the need for further treatment using unblinded information.

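### Table 2 gives an rTMS train structure and a session duration that cannot both be right

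*Protocol article*

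**What the plan says.** The rTMS specification is Table 2 of the protocol article, under Acupuncture technique for the experimental group. The text introducing it presents the table as the summary of the main stimulation settings, pulse configuration among them. The rows that matter here are:

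- Session duration, given as 19 min 50 s
- "Total pulses/session", given as 2,000
- "Inter-train interval", given as 10 s
- "Train duration", also given as 10 s
- "Trains per session", given as 20
- Frequency, given as 10 Hz
- The pulse count of a single train, given as "1 pulses per train"

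Both control arms point back to this specification. For control group 1: "The rTMS protocol (parameters, site, and schedule) is identical to that described for the experimental group". For control group 2: "The rTMS protocol (parameters, site, and schedule) will be identical to that described for the experimental group". Nothing else in the article gives a pulse pattern or an rTMS session length against which the table could be checked.

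**The concern.** Frequency, number of trains, train length, gap and total pulses are tied together by simple arithmetic, and so is the run time. Two of the printed rows do not fit the rest. The first, pulses per train, could be dismissed as a typing slip. The second, session duration, is about three times what the other rows imply, and it matches a different schedule exactly. The table may therefore have been assembled from two schedules.

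This is the only description of a treatment meant for all 126 planned participants. A therapist programming the device, an auditor checking implementation (foreseen under Quality control) or a group repeating the trial cannot be sure from the document what is to be delivered. The protocol also provides for a seizure during treatment: "in case of a seizure (despite excluding high-risk participants), stimulation will be stopped immediately". That is a further reason for the stimulation pattern to be unambiguous, although the document gives no risk by schedule and none is claimed here.

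**Working it through.** **Inputs**, all from Table 2: frequency 10 Hz; 20 trains; train duration 10 s; inter-train interval 10 s; total 2,000 pulses; pulses per train 1; session duration 19 min 50 s = 19 × 60 + 50 = 1,190 s.

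**Total pulses.** Pulses per train = frequency × train duration = 10 × 10 = 100. Total = 20 × 100 = 2,000. The stated total is reproduced.

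**Pulses per train.** The table says 1, but the figure is 100. With 1 pulse per train the total would be 20 × 1 = 20, smaller than the stated total by a factor of 100.

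**Session duration.** Duration = trains × train duration + gaps × interval.

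- With 19 gaps: 20 × 10 + 19 × 10 = 390 s = 6 min 30 s.
- With a 20th gap counted after the last train: 400 s = 6 min 40 s.

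The stated 1,190 s is reproduced under neither count; 1,190 / 390 = 3.05.

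**What would give 19 min 50 s with 2,000 pulses at 10 Hz?** Stimulation time is 2,000 / 10 = 200 s in any schedule, which leaves 1,190 − 200 = 990 s of gaps.

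- Keep the 10 s gap: 990 / 10 = 99 gaps, so 100 trains. Each lasts 200 / 100 = 2 s and holds 20 pulses. Check: 100 × 2 + 99 × 10 = 1,190 s, exact.
- Keep 20 trains of 10 s: the gap becomes 990 / 19 = 52.1 s (49.5 s with 20 gaps), against 10 s stated.

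**The candidate schedules side by side:**

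| Schedule | Trains × length | Gap | Pulses per train | Run time | Stimulating share | Table 2 rows changed |
|---|---|---|---|---|---|---|
| A | 20 × 10 s | 10 s | 100 | 390 s | 200/390 = 51.3% | 2 (pulses per train, session duration) |
| B | 100 × 2 s | 10 s | 20 | 1,190 s | 200/1,190 = 16.8% | 3 (trains, pulses per train, train duration) |
| C | 20 × 10 s | 52.1 s | 100 | 1,190 s | 200/1,190 = 16.8% | 2 (pulses per train, gap) |

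A and B differ by 10/2 = 5 in train length, and by 51.3/16.8 = 3.05 in the share of time spent stimulating.

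The run time can also be matched by giving up the total. For example, 60 trains of 10 s with 10 s gaps take 60 × 10 + 59 × 10 = 1,190 s, but deliver 6,000 pulses.

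**Could the session include set-up?** Schedule A would need 1,190 − 390 = 800 s = 13 min 20 s without stimulation. The table states no such allowance.

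**The case against.** The best defence is that Table 2 is one sound schedule with two poor entries. A train of 1 pulse is no train at all, and the figure may be a typing or text-extraction slip for 100. The rows for frequency, trains, train length and total agree exactly. Schedule A keeps them all, along with the gap, whereas B overwrites two explicit and mutually consistent rows and is a reconstruction: no row states 100 trains, 2 s or 20 pulses. Session duration is also not defined as the time from first to last pulse. The same section gives about 40 min for an acupuncture session with 30 min of needle retention, so the authors do use the word session for more than the core procedure.

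Much of this is fair. The pulse row alone would be a trivial correction, and A is a natural first reading. But the defence leaves the duration row unexplained. An allowance of 13 min 20 s, twice the stimulation run itself, is long. The motor threshold is measured before the first session, so it does not explain a fixed allowance at every session. A figure given to the nearest 10 s that matches B exactly looks like a device run time. Counting changed rows does not decide the matter either, since C changes two rows, as A does.

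It is also fair to say that the consequences are limited. rTMS is the same in every arm, and the device may already be programmed correctly.

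**Conclusion.** The point stands, and Table 2 should be corrected. Pulses per train is wrong by a factor of 100 against the other rows, and the session duration is about three times the run time those rows imply. No other part of the article resolves the conflict.

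No dose error is shown. Taking 10 Hz and 2,000 pulses as correct is an assumption, supported by 20 × 10 s × 10 Hz giving exactly that total. The fivefold difference in train length holds only if B is the alternative to A. The threefold difference in stimulating share holds for either B or C.

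The error does not bias the between-arm contrasts and does not affect the sample size or the analysis. Its cost falls on treatment fidelity, auditing and replication.

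**What to change.** Read the schedule off the programmed device, have the person responsible for rTMS confirm that it is the intended one, and correct Table 2 once for all three arms:

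- If A is intended, keep 20 trains of 10 s with 10 s gaps, and state 100 pulses per train and 6 min 30 s.
- If B is intended, keep the 10 s gap and 19 min 50 s, and state 100 trains of 2 s with 20 pulses each.
- If 20 trains of 10 s over 19 min 50 s is intended, state 100 pulses per train and the true gap (about 52 s).
- If 19 min 50 s includes set-up, say so and give the stimulation time separately.

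This should be settled before the first participant is treated. If treatment has already begun, report the schedule actually delivered. The cost is a corrected table and one check of the device programme; design, sample size and analysis stay as they are.

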**Methods:**

This randomized controlled trial will randomly assign eligible participants to three groups in a 1:1:1 ratio: the experimental group (YLDJJ acupuncture + rTMS), the control group 1 (conventional acupuncture + rTMS), and the control group 2 (sham acupuncture + rTMS). The participants will be aged 18–80 years old, with CRPS-I developing after stroke and meeting the specific inclusion criteria. The intervention measures will be administered once daily for 20 days. Pain intensity, assessed using the visual analogue scale (VAS), will be measured at baseline, on days 10 and 20, and at 1 and 3 months after treatment completion. Secondary outcome measures include motor function, muscle tone, shoulder range of motion, activities of daily living, thermal asymmetry, and neuroplasticity-related indicators. The sample size will be 126 participants, accounting for a 20% dropout rate.

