#### Outcomes

The efficacy of the intervention will be evaluated by two independent research assistants blinded to group assignment, using pre-specified primary and secondary outcomes. Assessments will be conducted at baseline (before the first treatment), on days 10 and 20, and 1 and 3 months after the end of treatment (Table 4).

**Table 4 tab4:** Schedule of outcome assessments across study time points.

Item	Timepoint				
	Baseline	Treatment period		Follow-up period	
		10 day	20 day	1 month	3 month
Enrolment					
Screening	√				
Signed informed consent	√				
Randomization	√				
Intervention					
Yuan-Luo Da-Jie-Jing acupuncture + rTMS					
Conventional acupuncture + rTMS					
Sham acupuncture + rTMS					
Assessment					
Primary outcome					
VAS	√	√	√	√	√
Secondary outcome					
Brunnstrom	√	√	√	√	√
Modified ashworth	√	√	√	√	√
AROM	√	√	√	√	√
Simplified Fugl-Meyer	√	√	√	√	√
Improved Barthel index	√	√	√	√	√
Infrared thermal imaging	√	√	√	√	√
RS-fMRI	√	√	√	√	√
CRPS-specific severity	√	√	√	√	√
Other measures					
Blinding assessment		√	√	√	√
Additional treatment		√	√	√	√
Rescue medication use		√	√	√	√
Adverse event		√	√	√	√

VAS, Visual Analogue Scale; rTMS, Repetitive transcranial magnetic stimulation; AROM, active range of motion; RS-fMRI, Resting-state functional magnetic resonance imaging.

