#### Analysis populations

The intention-to-treat (ITT) population will include all randomized participants.

The per-protocol (PP) population will comprise participants who complete at least one intervention session and provide primary outcome data at the end of treatment (day 20).

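### Acupuncture is scheduled over 4 weeks but rTMS over 20 days in a row, so it is not fixed how much treatment the day-20 VAS follows or when treatment ends

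*Protocol article*

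**What the plan says.** All references are to the protocol article.

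- **Acupuncture, experimental group** (Acupuncture technique): "Sessions will be conducted once daily, 5 days per week, for a total of 20 sessions over 4 weeks".
- **rTMS** (Table 2, same section): "Once daily for 20 consecutive days".
- **Both components together** (Abstract, Methods): "The intervention measures will be administered once daily for 20 days". The Discussion likewise speaks of a 20-day regimen.
- **Control group 1**: "treatment schedule (once daily, 20 sessions) will be standardized to match the procedures in the experimental group", with the rTMS protocol also identical.
- **Control group 2**: "The session frequency and duration (once daily, 20 sessions) will be identical to the other groups", again with identical rTMS.
- **Visit times** (Outcomes section): "Assessments will be conducted at baseline (before the first treatment), on days 10 and 20, and 1 and 3 months after the end of treatment". The same time points appear in Table 4.
- **Day 20 as the end of treatment**: under Analysis populations, PP members must "provide primary outcome data at the end of treatment (day 20"). Exclusion from PP analysis also removes anyone without a VAS at day 20, which it labels post-treatment.
- **A different wording** (Data collection and management): the two on-treatment collections are placed on the tenth and twentieth days of treatment.

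No section says how the acupuncture and rTMS schedules fit together, or whether day 20 is counted in calendar days or treatment days.

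**The concern.** The trial tests a combined treatment. One component is spread over 4 weeks and the other over 20 days in a row, and the plan treats day 20 as the end of both. These statements cannot all hold.

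The VAS is the primary outcome, and between-group differences are estimated at each time point, including day 20. Acupuncture is the only component that differs between arms; rTMS is common to all three. The number of acupuncture sessions behind the day-20 VAS therefore decides what that contrast means: the effect of a full course, or of about three quarters of one. The same ambiguity reaches two other rules: the day-20 VAS required for PP membership, and the treatment-end date from which the 1- and 3-month visits run. Staff working from different sections could also book the same visit on different dates.

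**Working it through.** **Inputs**
- Acupuncture: 5 sessions per week, 20 sessions, 4 weeks (Acupuncture technique).
- rTMS: 20 days in a row (Table 2).
- On-treatment visits: days 10 and 20 (Outcomes, Table 4).
- Assumption for the count: day 1 is the first session and acupuncture is given Monday to Friday.

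**Step 1. The plan's own total.** 5 × 4 = 20 sessions, as stated. The acupuncture schedule is consistent in itself.

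**Step 2. Acupuncture sessions by calendar day.**

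| First session | Session days | By day 10 | By day 20 | Last session |
|---|---|---|---|---|
| Mon | 1-5, 8-12, 15-19, 22-26 | 8 | 15 | day 26 |
| Tue | 1-4, 7-11, 14-18, 21-25, 28 | 8 | 14 | day 28 |
| Wed | 1-3, 6-10, 13-17, 20-24, 27-28 | 8 | 14 | day 28 |
| Thu | 1-2, 5-9, 12-16, 19-23, 26-28 | 7 | 14 | day 28 |
| Fri | 1, 4-8, 11-15, 18-22, 25-28 | 6 | 14 | day 28 |

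At day 20 the share delivered is 14/20 = 70% to 15/20 = 75%, so 5 or 6 sessions remain. The last session is 26 − 20 = 6 or 28 − 20 = 8 days after the visit.

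**Step 3. rTMS by calendar day.** 10 of 20 by day 10 and 20 of 20 by day 20.

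**Step 4. Sensitivity to the assumptions.**
- Any five days in each study week: two full weeks give 10 sessions. Days 15 to 20 are six of the seven days of week three, so they hold 4 or 5 of its 5 sessions, which makes 14 or 15 by day 20. Week four is days 22 to 28, so its fifth session falls no earlier than day 26.
- VAS taken before that day's session: 13 to 15.
- First session counted as day 0: 15 for every starting weekday.

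The shortfall remains in each case.

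**Step 5. Day 20 read as the twentieth treatment day.** For acupuncture this is the last session, on calendar day 26 or 28. For rTMS it is calendar day 20. The shortfall disappears if the visit follows the acupuncture count, but the two components then give dates 6 or 8 days apart.

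**Step 6. Both schedules followed literally.** By day 20, rTMS has been given 20 times and acupuncture 14 or 15 times. So 5 or 6 rTMS sessions fall on days without acupuncture, and 5 or 6 acupuncture sessions follow after rTMS has ended. The end of treatment is then day 20 for one component and day 26 or 28 for the other.

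**The case against.** The best reply is that day 20 was never meant as a calendar day. Data collection and management refers to days of treatment. Both PP definitions equate day 20 with completed treatment, and the control-arm sections speak only of once-daily treatment and 20 sessions. Read this way, the acupuncture schedule, the visits and the PP condition agree, and the conflict shrinks to the run of consecutive days in Table 2 and the loose 20-day label in the Discussion. This reading is possible, so the 70-75% figure is conditional. It is not decisive: the abstract, Outcomes and Table 4 give bare day numbers, and step 5 shows that it still yields two dates while Table 2 stands.

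It can also be said that the schedules belong to two components and could both be followed, since no section requires same-day pairing. That is literally true. But the abstract gives one schedule for both, and treatment would still have two end dates.

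Several stronger readings are tempting and are not supported:
- *The follow-up visits are anchored to day 20.* They are not. The abstract and Outcomes run them from the end of treatment; they become ambiguous only because that end may have two dates.
- *The whole PP rule depends on the calendar.* The exposure criterion in Exclusion from PP analysis counts sessions and is unaffected. Only the day-20 VAS condition is touched.
- *Day 20 is the main efficacy visit.* No section says so. Day 20 is singled out only for PP membership.
- *The contrast is diluted or one arm is favoured.* The schedule is the same in all arms, so there is no differential bias. Dilution is plausible if the VAS is taken before acupuncture ends, but nothing in the document allows a figure.

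**Conclusion.** The protocol contradicts itself on the treatment schedule, and the time points built on it are therefore not fixed. If day 20 is a calendar day and acupuncture is given 5 days a week, the VAS labelled end of treatment is taken after 14 or 15 of 20 acupuncture sessions, 6 to 8 days before acupuncture ends, with rTMS complete. If day 20 is a treatment day, the visit date depends on which component is counted. Either way, the meaning of the day-20 contrast, the day-20 VAS condition for PP membership and the starting date for the 1- and 3-month visits are unclear by about a week.

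A reader might infer that the visit will certainly fall mid-treatment, or that the trial's result is biased. The document supports neither: the first depends on the calendar-day reading, and the ambiguity is common to all three arms. The contradiction itself depends on neither, and inconsistent visit timing cannot be repaired once the data are collected.

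**What to change.** 1. Reconcile the schedule statements in the abstract (Methods), the Acupuncture technique text, Table 2 and the Discussion. Which schedule applies is for the clinical lead to decide. The control-arm sections fit either schedule and will follow the experimental arm.
2. Define the on-treatment assessments by session: after session 10 and after session 20, or on the planned last-session date for participants who stop early. Use this definition in the abstract, Outcomes with Table 4, Exclusion from PP analysis, Data collection and management, and Analysis populations.
3. State one treatment-end date that covers both components, and run the 1- and 3-month visits from it.

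The cost is protocol wording, visit labels on the case report form and a registry update, best made before enrolment. Sample size and the analysis model do not change.
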